# Radioembolisation with yttrium‒90 microspheres versus sorafenib for treatment of advanced hepatocellular carcinoma (SARAH): study protocol for a randomised controlled trial

**DOI:** 10.1186/1745-6215-15-474

**Published:** 2014-12-03

**Keywords:** Advanced hepatocellular carcinoma, Radioembolisation (RE), SIR-Spheres™ microspheres, Sorafenib

## Abstract

**Background:**

Untreated advanced hepatocellular carcinoma (HCC) is linked to poor prognosis. While sorafenib is the current recommended treatment for advanced HCC, radioembolisation (RE; also called selective internal radiation therapy or SIRT) with yttrium-90 microspheres has shown efficacy in cohort studies. However, there are no head-to-head trials comparing radiation therapy with yttrium-90 microspheres and sorafenib in advanced HCC. The SARAH trial has been designed to compare the efficacy and safety of sorafenib therapy and RE using yttrium-90 resin microspheres (SIR-Spheres™; Sirtex Medical Limited, North Sydney, Australia) in patients with advanced HCC. Quality of life (QoL) and cost-effectiveness will also be compared between therapies.

**Methods/Design:**

SARAH is a prospective, randomised, controlled, open-label, multicentre trial comparing the efficacy of RE with sorafenib in the treatment of patients with advanced HCC. The trial aims to recruit adults with a life expectancy of >3 months, Eastern Cooperative Oncology Group (ECOG) performance status ≤1, and: advanced HCC according to the Barcelona criteria (stage C) or recurrent HCC after surgical or thermoablative treatment who are not eligible for surgical resection, liver transplantation or thermal ablation; or two rounds of failed chemoembolisation. Patients will be randomised 1:1 to receive either RE or sorafenib 400 mg twice daily. All patients will be monitored for between 12 and 48 months following start of treatment. The primary endpoint of the SARAH trial is overall survival (OS). Secondary endpoints include: adverse events, progression-free survival at 6 months; tumour response rate; general or liver disease-specific QoL scores; and cost of each treatment strategy. Assuming an increase in median OS of 4 months with RE versus sorafenib therapy, randomising at least 400 patients (200 in each treatment arm) will be sufficient for 80% power and a bilateral alpha risk of 5%; therefore, 440 patients will be enrolled to allow for 10% loss of patients due to ineligibility.

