### Trial assessments

The last enrolled patient will be followed up for 12 months after the start of treatment (D0). All other patients will be followed up until the final visit of the last enrolled patient. Patients will therefore be followed up for a maximum of 48 months and a minimum of 12 months following start of treatment. All patients will be assessed by the schedule summarised in Table 2. Treatment will be discontinued if the patient withdraws consent, if the treating physician deems it necessary for medical reasons or if a serious adverse event occurs - after discontinuation, patients should be assessed by CT as soon as possible to assess response to treatment.

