### Sample size calculation and statistical considerations

Based on OS data with sorafenib from the SHARP study[6] and with yttrium-90 RE reported in the literature[9, 11–15], the number of patients required for randomisation to detect a clinically relevant increase (4 months) in OS time with RE versus sorafenib was determined as 400 patients (200 patients in each treatment arm). This translates to an expected median OS time of 10.7 months in the sorafenib group and 15 months in the RE group, with an accrual period of 24 months and follow-up of 12 months. These guarantee a power of 80% with a bilateral alpha risk of 5%. Estimating that up to 10% of patients that are recruited will not fulfil the criteria of eligibility for randomisation, we aimed to enrol 440 patients.

A Data Monitoring Committee (DMC) will regularly review the toxicity data to assess the safety profile of the treatment (including serious adverse events and mortality). The first intermediate analysis will take place once 30 patients have been followed up for at least 2 months in each treatment arm, after which the DMC will convene every 6 months.

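### The 80% power is claimed for a 4-month gain in median OS but calculated for 4.3 months, and the 48-month maximum follow-up does not fit 24 months' accrual

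*Protocol article*

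**What the plan says.** **Effect size.** The abstract (Methods/Design) bases the trial on a 4-month gain: "Assuming an increase in median OS of 4 months with RE versus sorafenib therapy, randomising at least 400 patients" is given as enough for 80% power at a two-sided 5% level. The section on sample size calculation also names a "clinically relevant increase (4 months) in OS time with RE versus sorafenib" as the target. Its next sentence equates that target with an "expected median OS time of 10.7 months in the sorafenib group and 15 months in the RE group", and claims 80% power for those medians.

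**Timeline.** The same section bases the calculation on a design "with an accrual period of 24 months and follow-up of 12 months". The overview of trial design also gives 24 months for recruitment. The section on trial assessments follows the last enrolled patient for 12 months from the start of treatment and ends everyone else's follow-up at that patient's final visit. It then concludes: "Patients will therefore be followed up for a maximum of 48 months and a minimum of 12 months following start of treatment". The abstract gives the same range of 12 to 48 months.

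**The concern.** Two sets of stated figures do not agree.

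- The medians used in the calculation differ by 15 − 10.7 = 4.3 months, not 4. A 4-month gain over 10.7 months is a median of 14.7 months. That is a smaller effect and needs more deaths for the same power.
- With 24 months' accrual and a trial that ends 12 months after the last patient starts treatment, the first patient can be followed for about 36 months. The 48-month maximum is presented as a consequence of the follow-up rule, but it does not follow from it.

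The stake is what the trial can be said to have been powered for. If the result is null, a reader who relies on the abstract would take a 4-month gain as the effect the trial had an 80% chance of detecting. The expected number of deaths, and so the power, also depends on which timeline holds.

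**Working it through.** **Inputs from the protocol article.** Two-sided alpha 5% and power 80% (abstract and sample size section); control median 10.7 months and RE median 15 months (sample size section); 200 patients per arm; accrual A = 24 months and follow-up after the last entry F = 12 months. The alternative RE median of 14.7 months is 10.7 + 4. The alternative accrual of 36 months is 48 − 12.

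**Assumptions, because the article does not give them.** Exponential survival, uniform accrual, no loss to follow-up.

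**Formulas.** With hazard λ = ln 2 / median:

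- Probability of death by the end of the trial: P = 1 − [exp(−λF) − exp(−λ(A+F))] / (λA)
- Expected deaths: D = 200 × (P for sorafenib + P for RE)
- Deaths needed (Schoenfeld, 1:1): 4 × (1.960 + 0.842)² / (ln HR)²
- Power: Φ(√D × |ln HR| / 2 − 1.960)

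**Step 1: reproduce the stated figure (10.7 versus 15, 24 + 12 months).** HR = 10.7/15 = 0.713. Deaths needed: 275.1, so 276. P = 0.7668 and 0.6530, so D = 200 × 1.4198 = 284. Power = 81.2%. Freedman's formula gives 80.5% and a log-rank simulation of 10,000 runs gives 80.1%. Patients needed for 80% are 389 to 396. The stated 400 at 80% is reproduced.

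**Step 2: a gain of exactly 4 months, same timeline.** HR = 10.7/14.7 = 0.728. Deaths needed: 311.2, so 312, which is 36 (13%) more than for 4.3 months. P = 0.7668 and 0.6600, so D = 285. Power = 76.5%. Freedman gives 75.8%, Lachin–Foulkes 76.0% and simulation 76.9%.

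**Step 3: maximum follow-up.** 24 + 12 = 36 months. For 48 months, accrual would have to be 48 − 12 = 36 months, a figure that appears nowhere in the article. Treatment with RE starts in the second to fifth week after randomisation (Treatments section). A lag of that size cannot account for 12 months.

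**Step 4: all four combinations, 400 randomised.**

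| RE median (gain) | Accrual + follow-up | Maximum follow-up | Expected deaths | Deaths needed for 80% | Power |
|---|---|---|---|---|---|
| 15 (4.3 months) | 24 + 12 | 36 | 284 | 276 | 81.2% |
| 14.7 (4 months) | 24 + 12 | 36 | 285 | 312 | 76.5% |
| 15 (4.3 months) | 36 + 12 | 48 | 308 | 276 | 84.3% |
| 14.7 (4 months) | 36 + 12 | 48 | 310 | 312 | 79.8% |

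A power of about 80% with 400 patients fits the first and last rows. The 4-month gain on the stated 24 + 12 timeline is the second row.

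**The case against.** The strongest reply is that the calculation itself is right. The sample size section states its medians and timeline, and these give 400 patients at 80%. The 4 months is then a rounding of 4.3, with the exact inputs in the next sentence. Most of this stands: there is no error in the number of patients, and rounding may well be the explanation. But the rounded figure is the one called clinically relevant and the one the abstract attaches power to, without giving the medians. On the 24 + 12 timeline the rounding is worth 81.2 − 76.5 = 4.7 percentage points.

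A second reply is that the 76% belongs to a combination the abstract does not state. The abstract gives no accrual period, only 12 to 48 months of monitoring, and with 36 + 12 months a 4-month gain has 79.8% power. This also stands, so the 76% must be reported as conditional on the 24 + 12 timeline. That timeline is nevertheless the one in the overview and in the calculation.

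A third reply is that 440 patients, if all were randomised, would give 80.3% at 4 months on 24 + 12 months. That is correct, but the extra 40 are an allowance for patients found ineligible for randomisation.

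None of these replies explains 48 months against 36. A longer accrual would raise power, so this discrepancy does not threaten the planned power at the stated medians. It remains a contradiction about how long the trial runs.

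**Conclusion.** Two statements are wrong as written. The 80% power is attached to a 4-month gain, although the calculation supports it for 4.3 months; on the stated 24 + 12 month timeline, power for exactly 4 months is about 76% (75.8% to 76.9% across methods), with about 285 deaths expected against 312 needed. And a 48-month maximum follow-up does not follow from 24 months' accrual plus 12 months; about 36 months does. The power figures rest on exponential survival, uniform accrual and no loss to follow-up.

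A reader might infer more than this, without support from the document:

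- *That 400 patients are too few.* The number is reproduced from the stated medians and timeline.
- *That figures from two versions of the design were merged.* The table is compatible with that, but the article describes one design and gives no such history.
- *That the enrolment allowance leaves the trial short.* 440 less 10% is 396, slightly under 400, but power at 10.7 versus 15 months is then still 80.8%, and the allowance is for up to 10%.
- *That the final analysis should wait for a number of deaths.* The design ends by calendar, at the last patient's final visit, and the contradiction can be resolved without an event target.

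**What to change.** 1. **Effect size.** In the abstract and in the sample size section, state the detectable gain as 4.3 months (10.7 versus 15 months, HR 0.713), with about 284 deaths expected and about 81% power. Alternatively, keep 4 months (10.7 versus 14.7, HR 0.728) and state power of about 76% for 24 months' accrual and 12 months' follow-up.
2. **Timeline.** Make the abstract, the overview, the trial assessments section and the sample size section agree: either 24 months' accrual with a maximum of about 36 months, or 36 months' accrual with a maximum of 48. If the longer timeline is the intended one, restate power to match: about 84% for 4.3 months or about 80% for 4 months.
3. **Assumptions.** Give the survival, accrual and loss assumptions beside the restated power, so that the figure can be checked.

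The cost is a few lines of text. No extra patients and no event-count condition are needed.

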**Discussion:**

The SARAH trial is the first randomised head-to-head study to compare RE with sorafenib in advanced HCC, and will establish the potential role of RE in HCC treatment guidelines.

**Trial registration:**

ClinicalTrials.gov identifierNCT01482442, first received 28 November 2011

**Electronic supplementary material:**

The online version of this article (doi:10.1186/1745-6215-15-474) contains supplementary material, which is available to authorized users.

## Background

The prevalence and incidence of hepatocellular carcinoma (HCC) is highly variable in different regions of the world but the burden is predicted to increase in the coming years[1]. In developed countries, early diagnosis of HCC is possible in 30 to 60% of patients, and as a result, HCC is often diagnosed in the advanced stage of disease (stage C of the Barcelona Clinic Liver Cancer classification – that is, ECOG performance status 1 to 2, portal invasion or extrahepatic spread, and Child-Pugh A-B). Curative treatment (by surgical resection, liver transplantation or thermoablative treatment) is possible only in a limited proportion of these patients[2], and many cases of HCC progress to an advanced stage following locoregional treatment. In patients with untreated advanced HCC, the prognosis is poor, with a median survival time of approximately 5 to 7 months, although this varies depending on Child‒Pugh score[3–5].

The pivotal Sorafenib Hepatocellular carcinoma Assessment Randomized Protocol (SHARP) trial showed that sorafenib (Nexavar™, Bayer HealthCare Pharmaceuticals, Berlin, Germany) treatment significantly increased median overall survival (OS) time by approximately 3 months versus placebo (10.7 months versus 7.9 months, respectively; *P* <0.001) in patients with advanced HCC[6]. These findings were subsequently confirmed in a randomised controlled trial in the Asia-Pacific, which showed OS of 6.5 months in the sorafenib arm versus 4.2 in the placebo arm (*P* <0.014)[7]. As a result of these data, sorafenib is the current recommended first-line treatment for advanced (Barcelona stage C) HCC[2]. However, while sorafenib increased OS in the SHARP study, it did not improve median time to symptomatic progression, and was associated with an overall adverse‒effect incidence of 80%. Adverse events experienced by >5% of patients in the SHARP trial included diarrhoea (13.1%), asthenia (7.4%), hand-foot skin reaction (7.0%), and erythema or desquamation (5.4%); dose reductions and treatment interruptions due to adverse effects occurred in 26% and 44% of cases, respectively[6]. As such, there is a medical need for the study of alternative treatment options for advanced HCC.

Radioembolisation (RE; also called selective internal radiation therapy or SIRT) with SIR-Spheres™ (Sirtex Medical Limited, North Sydney, Australia), which contain the β-emitter yttrium-90, is one potential alternative treatment of advanced HCC. RE enables targeted delivery of radiation to the tumours, while the surrounding liver parenchyma is largely spared. A recent meta‒analysis showed a high response rate to yttrium‒90 RE in HCC patients[8]. Population disparity prevented assessment of OS in this meta-analysis but cohort studies of patients with HCC receiving yttrium‒90 RE report median OS between 7 and 26.3 months[9–18]. Collectively, these data suggest that the use of RE for advanced HCC warrants further investigation, and might improve median OS with fewer side effects and/or better quality of life (QoL) compared with sorafenib.

To the authors’ knowledge, no controlled, prospective trials have been published on the efficacy of RE in HCC patients. For this reason, the SorAfenib versus Radioembolisation in Advanced Hepatocellular carcinoma (SARAH) trial has been designed as a prospective, randomised, open-label, multicentre trial to compare the OS in patients with advanced HCC receiving either RE with SIR-Spheres™ or sorafenib. Secondary objectives include comparisons between the treatment arms of other efficacy parameters, the safety profile and tolerability, QoL and cost-effectiveness.

## Methods/Design

The SARAH trial will be conducted in accordance with the Declaration of Helsinki and current good clinical practice guidelines, and all participating centres have obtained the relevant ethics committee approval before patient enrolment (see Additional file1).

### Eligible population

The inclusion and exclusion criteria for the SARAH trial are summarised in Table 1. Informed consent will be obtained from each participant.

**Table 1 Tab1:** **Patient eligibility criteria for SARAH trial**

Inclusion criteria	Exclusion criteria
• Written informed consent provided	• Other primary tumour except for basal cell carcinomas or superficial bladder cancers
• Aged ≥18 years	
• Histologically or cytologically confirmed diagnosis, or AASLD criteria for the diagnosis, of HCC and at least one measureable lesion on CT according to RECIST criteria	• Extrahepatic metastases except non-specific pulmonary tumours <1 cm and abdominal lymph nodes <2 cm
	• Previously treated advanced HCC (excluding chemoembolisation^*^)
• Patients not eligible for surgical resection, liver transplantation or thermoablation who have advanced HCC according to the Barcelona criteria (stage C), with or without portal invasion **OR** patients with recurrent HCC (new lesion in a different place) after surgical or thermoablative treatment who are not eligible for any other treatment; **OR** patients in whom chemoembolisation has failed after two rounds – treatment failure is defined as the absence of objective response in the treated nodule after two rounds (objective response according to the modified RECIST criteria and/or EASL criteria)	• Advanced liver disease with a Child-Pugh score > B7 or active digestive haemorrhage or encephalopathy or refractory ascites
	• Pregnant or breastfeeding women
	• Allergy to contrast agents
	• Contraindication to hepatic artery catheterisation, such as severe peripheral arterial disease precluding catheterisation
	• Mental illness or other psychological disorder affecting the informed consent
	• Patient unable or unwilling to comply with the treatment and follow-up required by the study
	• Unable to take oral medication
• ECOG performance status ≤1	
• Adequate haematological function: haemoglobin ≥9 g/100 mL, neutrophils ≥1,500/mm^3^, platelets ≥50,000/mm^3^	
• Adequate kidney function: creatinine <150 μmol/L	
• Bilirubin ≤50 μmol/l, AST or ALT ≤5 x ULN, INR ≤1.5	
• If liver cirrhosis, Child-Pugh A-B7	
• Affiliated to a social security scheme or beneficiary	

^*^Patients who have not responded to chemoembolisation but who meet the other selection criteria will be included in this study. AASLD, American Association for the Study of Liver Diseases; ALT, alanine aminotransferase; AST, aspartate transaminase; CT, computed tomography; EASL, European Association for the Study of the Liver; ECOG, Eastern Cooperative Oncology Group; HCC, hepatocellular carcinoma; INR, international normalised ratio; RECIST, response evaluation criteria in solid tumours; ULN, upper limit of normal.

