### Randomisation

Eligible patients will be randomised 1:1. The randomisation will be stratified by centre, Eastern Cooperative Oncology Group (ECOG) score (0 versus 1), the presence or absence of macroscopic vascular invasion seen on imaging (obstruction of the portal vein or its branches) and previous chemoembolisation failure. The list will be balanced by different sized blocks and randomly alternated. The data coordination centre will prepare the randomisation list before enrolment begins.

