### Statistical analysis

Results will be reported according to the Consolidated Standards of Reporting Trials (CONSORT) statement. An ITT analysis will be performed, keeping patients in their randomisation group and including protocol deviations. A ‘per-protocol’ sensitivity analysis will also be performed. A study flowchart will be provided, including the number of patients who: are eligible; are randomised to receive treatment; are followed up; withdraw from the study; and are lost to follow-up. Major protocol deviations and the reasons for withdrawal from the study will be described.

The Kaplan and Meier method will be used to calculate survival (OS and PFS). The comparison of survival rates at 12 months between the two treatment groups will be performed using the log rank test (Mantel-Haenszel version). In addition, the treatment effect, once adjusted for the stratified randomisation factors, will be calculated via: (1) a stratified log rank analysis; and (2) a Cox’s regression model.

The median survival times (OS and PFS) in both treatment groups will be calculated, along with the confidence interval associated with the difference or with the median survival time ratio[24].

Toxicity will be reported according to NCI CTCAE Version 3.0, with particular reference to the proportion of patients experiencing grade 3/4 toxicity in each treatment arm.

The objective response will be determined via the RECIST and modified (m)RECIST criteria, the EASL criteria for HCC, and the Choi criteria, and a comparison will be made between the two treatment groups using the ‘best response during follow-up’ criterion. The response rates will be calculated by comparing the number of patients who responded during follow-up (complete or partial response) with the total number of randomised patients in each group. The related confidence intervals will be calculated and compared between the two groups using Pearson’s chi-squared test.

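### The adjusted overall-survival analyses leave out baseline Child-Pugh status; adding it to the planned Cox model would be a nearly free gain in precision

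*Protocol article*

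**What the plan says.** All references are to the protocol article.

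- **Table 1 (eligibility).** One inclusion criterion reads "If liver cirrhosis, Child-Pugh A-B7". Cirrhosis is not required, so entry runs from no cirrhosis to B7.
- **Background.** The prognosis of untreated advanced HCC is called poor, "with a median survival time of approximately 5 to 7 months, although this varies depending on" the Child-Pugh score. No size is given, and A is not contrasted with B7.
- **Randomisation.** "The randomisation will be stratified by centre, Eastern Cooperative Oncology Group (ECOG) score (0 versus 1"); macroscopic vascular invasion and previous chemoembolisation failure complete the list.
- **Statistical analysis.** The OS comparison named first is an unadjusted log-rank test. Then: "In addition, the treatment effect, once adjusted for the stratified randomisation factors, will be calculated via" a stratified log-rank analysis and a Cox model. The covariate set is therefore stated, and Child-Pugh is not in it.
- **Sample size.** The number to randomise was "determined as 400 patients (200 patients in each treatment arm"). The survival assumption behind it is stated as "expected median OS time of 10.7 months in the sorafenib group and 15 months in the RE group". Patients are taken to enter over two years, and the last of them to be observed for one more year.

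**The concern.** The Discussion justifies stratifying by ECOG score and by vascular involvement on the ground that they are prognostic. The Background names Child-Pugh score as something on which survival depends, but the score is neither a stratum nor a covariate, and no reason is given. Its value has to be known before randomisation for every cirrhotic patient, because eligibility turns on it.

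Leaving a prognostic baseline variable out of a survival analysis lowers the power to detect a given treatment effect. It also leaves the realised estimate open to whatever difference in liver function arises between the arms by chance. If such a difference appears in this open-label trial, an adjustment named in advance is much more credible than one added after the data have been seen.

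**Working it through.** **1. The plan's own figure.** Inputs from the sample size section: medians 10.7 and 15 months, 24 months' accrual, 12 months' further follow-up, two-sided alpha 5%, power 80%.

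- Hazard ratio under exponential survival: 10.7/15 = 0.713, with log −0.338.
- Events (Schoenfeld): 4 × (1.960 + 0.842)² / 0.338² ≈ 276. Freedman's formula gives 281.
- Probability of death by the end of the study, with λ = ln 2/median: 1 − (e^(−12λ) − e^(−36λ))/(24λ) = 0.767 for sorafenib and 0.653 for radioembolisation (RE), mean 0.710.
- Patients: 276/0.710 = 389, or 281/0.710 = 396.
- At 400 patients: 400 × 0.710 = 284 events and 81.2% power.

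The stated 400 reproduces, with about one point of power to spare.

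**2. Power with and without Child-Pugh.** The article gives neither the expected share of B7 patients nor their excess hazard. *Assumed:* shares of 10%, 20% and 30%; death hazard ratios, B7 against the rest, of 1.5, 2 and 2.5. For each pair, 4,000 trials of 400 patients were simulated with exponential survival within each group, a within-group treatment hazard ratio of 0.713 and the mixed control median held at 10.7 months. Because both groups scale by the same factor, the mixed RE median is then 10.7/0.713 = 15 months, so both planning medians are kept. Each trial was analysed by the unadjusted log-rank test and by a log-rank test stratified by B7 status.

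| B7 share | B7 hazard ratio | Unadjusted | Stratified by B7 | Loss (points) |
|---|---|---|---|---|
| 10% | 1.5 | 80.7% | 81.5% | 0.8 |
| 10% | 2 | 78.6% | 79.9% | 1.2 |
| 10% | 2.5 | 77.7% | 80.0% | 2.3 |
| 20% | 1.5 | 80.7% | 81.0% | 0.4 |
| 20% | 2 | 77.6% | 80.2% | 2.6 |
| 20% | 2.5 | 74.2% | 78.9% | 4.7 |
| 30% | 1.5 | 79.9% | 81.7% | 1.8 |
| 30% | 2 | 77.0% | 80.8% | 3.9 |
| 30% | 2.5 | 72.0% | 79.3% | 7.3 |

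Losses were taken before rounding. The Monte Carlo standard error is about 0.65 points per power figure.

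**3. Validity.** With no treatment effect, the unadjusted test rejected in 4.3% to 5.5% of trials across the same nine settings.

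**4. Chance imbalance.** With 200 patients per arm, the standard deviation of the difference in B7 share is √(q(1 − q) × 2/200), that is 3.0, 4.0 and 4.6 points at q = 10%, 20% and 30%. An imbalance of 1.96 standard deviations shifts the unadjusted hazard ratio by a factor of about exp(1.96 × SD × ln HR_B7):

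- smallest: exp(1.96 × 0.030 × 0.405) = 1.02
- largest: exp(1.96 × 0.0458 × 0.916) = 1.09

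**5. Could it be a stratum instead?** The Overview of trial design gives 28 centres. The existing strata form 28 × 2 × 2 × 2 = 224 cells, or 400/224 ≈ 1.8 patients each. A two-level Child-Pugh factor would make 448 cells, or about 0.9 patients each.

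**The case against.** The case against acting has real force.

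- **The first-named test is untouched.** That test is the unadjusted log-rank; the adjusted analyses come in addition. A change to the Cox model improves only the adjusted estimate and its test. This stands.
- **The comparator is generous.** The table sets an analysis without covariates against one that uses Child-Pugh. The planned Cox model already carries ECOG, vascular invasion, chemoembolisation failure and centre. The increment over that model was not computed, and any correlation of Child-Pugh with those factors would shrink it. This stands.
- **The Background sentence is narrow.** It concerns untreated patients and the score in general. Table 1 admits only one point of class B, caps bilirubin and INR, and excludes encephalopathy and refractory ascites. The A-to-B7 contrast in this trial may be modest, and at a hazard ratio of 1.5 the loss is small. This stands.
- **It could be left to the analysis plan.** Adjusting for the stratification factors is conventional, and the article does not forbid further models. This stands only in part: the article does not leave the covariate set open, it names one. If the analysis plan, which is not at hand, already adds Child-Pugh, the point is closed.

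A reader might also infer that the hazard ratio will be biased. The documents and the check do not support that. Randomisation keeps the test valid, and chance imbalance is imprecision that the confidence interval already reflects. The slight move of an unadjusted hazard ratio towards 1 is non-collapsibility: marginal and conditional hazard ratios are different quantities.

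**Conclusion.** The point holds as a matter of efficiency. The covariate set named for the adjusted OS analyses omits a baseline measure that the article itself links to survival and that eligibility already requires. The loss is about 0.4 to 7 points of power, or about 1 to 4 at a B7 hazard ratio of 2. That rests on assumed B7 shares of 10-30% and hazard ratios of 1.5-2.5, and on a comparison with an analysis that has no covariates. Against the planned stratum-adjusted Cox model the gain is unknown and may be smaller.

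Two stronger readings should be resisted. Some unadjusted figures above fall below 80%, and a reader might conclude that the sample size statement ("These guarantee a power of 80% with a bilateral alpha risk of 5"%) is wrong. It is not wrong on its own inputs, and the shortfall depends wholly on assumptions from outside the document. A reader might also conclude that Child-Pugh should have been a randomisation stratum. With fewer than one patient per cell, that would be a poor remedy.

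**What to change.** In the Statistical analysis section, or in the analysis plan that implements it, prespecify the adjusted Cox model for OS as the randomisation factors plus baseline Child-Pugh status in three categories: no cirrhosis, A5-A6, B7. Take the value from the eligibility assessment. Table 2 lists a classification item at enrolment but does not define it, so it is a less secure source.

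Leave the randomisation, the unadjusted log-rank test and the stratified log-rank test unchanged.

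The cost is one sentence and two degrees of freedom, or one if two categories have to be merged. No new data are needed. The change must be fixed before outcome data by arm are examined, otherwise its value against chance imbalance is largely lost.
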